## Statistical Considerations and Data Analysis

### *Baseline analysis*

Data processing and statistical analysis will be performed on pseudonymized data, in a blinded way. No interim analysis will be performed.

Using baseline data, cross-sectional results will be provided on general comfort, QoL, pain intensity, pain interference, stress, anxiety, self-efficacy, and burden of caregivers for patients who receive IDD. In addition to describing this population, supervised and non-supervised machine learning techniques will be applied such as hierarchical clustering, mediation analysis and regression models to explore the relations between baseline variables.

### *Main analysis*

To evaluate and compare therapy effects, mixed model analysis will be used. The need for random intercepts and slopes will be assessed. Potential confounding variables, such as baseline stress and anxiety levels, will be taken into account in the analysis. Statistical as well as clinical significance differences will be defined at  $\alpha < 0.05$ . Additionally, based on baseline data, predictive modelling will be conducted to identify which patients will benefit the most from home-based refill procedures. This will involve the application of both supervised and unsupervised machine learning techniques (K-means clustering, decision trees, and Random Forest algorithms). All statistical analysis will be performed in SAS, SPSS and R.

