#### Primary outcome

The primary outcome of this study is patient comfort, selected specifically to determine whether HAH care provides benefits for patients with chronic non-cancer pain and spasticity. This concept is grounded in Kolcaba's mid-range theory of comfort, which defines comfort as "The immediate experience of being strengthened by having needs for relief, ease, and transcendence met in four contexts: physical, psychospiritual, sociocultural, and environmental, and it is so much more than the absence of pain" (50,51). Patient comfort is evaluated with the General Comfort Questionnaire (GCQ), a self-reported instrument consisting of 48 items that reflect the physical, spiritual, environmental and social dimension (50). Responses are rated on a four-point Likert scale ranging from "strongly disagree" to "strongly agree". Some items are reverse scored during data processing, with higher overall scores indicating greater levels of comfort (52).

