## **Study Design**

### Study Design and patient enrollment

The IMPROVE study is a randomized, controlled, cross-over trial to evaluate if intrathecal pump refills at home (Intervention) are better for patient comfort (Outcome) compared to intrathecal pump refills at the hospital (Control) in patients who receive IDD (Population). We will include at least 82 patients, who will each receive two refills in the outpatient clinic and two refills at home.

The physician will briefly explain the IMPROVE study to eligible patients. If the patient is interested, the researcher will explain the study concept and practical aspects of their potential participation. Additionally, the patients will be screened based on in- and exclusion criteria.

The researcher will explain the study to the patient, what's expected for them and what's in it for them. If the patient is positive about participation, IC and contact information will be provided. IC will be obtained on paper. After receiving a signed IC, the IC will be scanned and stored electronically after which the original paper version will be destroyed.

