#### Sample size calculation

The sample size calculation (G\*Power version 3.1.9.4) is performed on patient comfort, measured with the general comfort questionnaire, as primary efficacy outcome variable after 4 intrathecal pump refill procedures. True mean comfort responses are based on the study of Zhao et al. (2021) (98), and a common standard deviation is calculated based on three studies which resulted in a value of 16.01049 (98–100). This results in an effect size of  $f=0.3035623$ . To conduct a randomized clinical trial with 2 intrathecal pump refill procedures at home and 2 procedures in the outpatient clinic with estimated true mean comfort responses for the outpatient clinic refill of 78.47 and 88.78 for the refill at home, with a common standard deviation of 16.01049, and 85% power to detect differences in means at a 5% two-sided significance level, a total sample size of 82 patients is needed. This sample size considers a 20% loss to follow-up after 4 refill procedures.

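### The protocol defines clinical significance by the 5% significance level, so the label follows the p-value and not the size of the difference

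*Protocol*

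**What the plan says.** Protocol section 10.4.2 (Main analysis) announces a mixed model and then sets the criterion: "Statistical as well as clinical significance differences will be defined at" α < 0.05. The sentence is not limited to the primary outcome.

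The primary outcome is the General Comfort Questionnaire, "a self-reported instrument consisting of 48 items that reflect the physical, spiritual, environmental and social dimension" (section 6.3.1). Neither that section nor any other gives a minimal important difference, a responder threshold or a relevance margin, for the GCQ or for any secondary outcome.

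The only effect stated in GCQ points is the planning assumption in section 11.3: "estimated true mean comfort responses for the outpatient clinic refill of 78.47 and 88.78 for the refill at home". It is presented as an assumed true effect and is not called a clinical threshold. The same section plans for "85% power to detect differences in means at a 5% two-sided significance level". Section 7.1 gives the design: "We will include at least 82 patients, who will each receive two refills in the outpatient clinic and two refills at home".

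**The concern.** A significance level controls how often a null effect is called real. It carries no information about whether a difference is large enough for a patient to care. Whether p falls below 0.05 depends on the number of patients and the precision of the measurement as well as on the effect. Using it to define clinical significance therefore fails in both directions: a small, precisely estimated difference earns the clinical label, and a large, imprecisely estimated one is refused it.

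What is at stake is how the results are described. The primary objective is to show that home refills are better for comfort. Comfort is self-reported by patients who cannot be blinded to location (section 7.3), so a reader will want to know how large a benefit is and not only that it differs from zero. The rule as written answers the first question with the answer to the second.

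**Working it through.** **Inputs from the protocol**
- Means 78.47 and 88.78, so a planned difference of 88.78 − 78.47 = 10.31 points (section 11.3).
- SD: "with a common standard deviation of 16.01049" (section 11.3); effect size f = 0.3035623.
- N: "a total sample size of 82 patients is needed"; "This sample size considers a 20% loss to follow-up after 4 refill procedures". Completers: 82 × 0.80 = 65.6, taken as 65.
- Two home and two hospital scores per patient (section 7.1).

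**Assumptions not in the protocol**
- Within-patient correlation ρ: not stated, so a range is shown.
- Compound symmetry, and no period or carryover effect.
- At first, no variation of the treatment effect between patients.

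**1. The plan's own figure.** For a repeated-measures ANOVA with a between-group factor, the noncentrality is λ = f²·N·m / (1 + (m − 1)ρ). With two groups, m = 4, an assumed ρ = 0.5 and N = 64, λ = 0.09215 × 64 × 4 / 2.5 = 9.44, which gives power 0.856. Then 64 / 0.80 = 80, within two patients of 82. With m = 3 the number is 68, and 68 × 1.2 = 81.6, rounded up to 82. So 82 is approximately recovered from a between-group formula; the protocol does not say which options were used.

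**2. Precision of the comparison actually made.** Per patient, take the mean of two home scores minus the mean of two hospital scores. Each mean has variance SD²(1 + ρ)/2, and their covariance is ρ·SD². The difference therefore has variance SD²(1 + ρ) − 2ρ·SD² = SD²(1 − ρ). With 65 completers, power for 10.31 points exceeds 99.9% for every ρ from 0 to 0.9, so p < 0.05 is reached well below 10.31.

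**3. Smallest observed difference with p < 0.05:** t(0.975, 64) × SD × √((1 − ρ)/65), with t(0.975, 64) = 1.998.

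| ρ | Points | In SD units | Share of 10.31 |
|---|---|---|---|
| 0 | 3.97 | 0.25 | 39% |
| 0.5 | 2.81 | 0.18 | 27% |
| 0.7 | 2.17 | 0.14 | 21% |

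If all 82 patients complete, the three values are 3.52, 2.49 and 1.93 points.

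**4. Allowing the treatment effect to vary.** Section 10.4.2 leaves random slopes open. With an assumed between-patient SD of the effect of 10 points, the standard error is √((SD²(1 − ρ) + 10²)/65).
- ρ = 0.5: √((128.17 + 100)/65) = 1.874, times 1.998 = 3.74 points.
- ρ = 0.7: √((76.90 + 100)/65) = 1.650, times 1.998 = 3.30 points.

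**5. How often the label would be given.** With 65 completers and no variation in the effect, a true difference of 3 points (3 / 16.01 = 0.19 SD) reaches p < 0.05 with probability 0.56 at ρ = 0.5 and 0.78 at ρ = 0.7. Under the stated rule each such result is called clinically significant.

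**6. The other direction.** For any outcome, an observed difference smaller than about twice its standard error misses p < 0.05. The rule then calls it not clinically significant, whatever its size.

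**The case against.** The strongest reply is that nothing operational hangs on the sentence. No test, estimate, decision rule or sample size uses the term clinical significance, and the primary mixed-model comparison is the same with or without it. Relevance thresholds for particular instruments also often sit in a statistical analysis plan, which is not at hand. The first part stands and limits the severity. The second does not remove the point: the protocol does not leave the definition open but states one, and the one it states is wrong.

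A reader might infer three stronger things that the documents do not support.
- *That trivial differences would be declared important.* No minimal important difference for the GCQ is given, so the documents cannot show that 2 to 4 points is trivial. They show only that it is well below an assumed true effect.
- *That the label would carry a reimbursement claim.* Section 10.4.3 addresses value through incremental cost-effectiveness ratios with bootstrapping and acceptability curves, a Markov model and a discrete choice experiment. None of these uses the significance label.
- *That across the twelve or so secondary outcomes a false clinical claim is close to an even chance.* The calculation 1 − 0.95^12 = 0.46 assumes independent tests. These outcomes come from the same patients and are related. Not all are repeated home-hospital tests either: preference is asked once, after the fourth refill, and expenditure has its own analysis. Multiplicity is also a separate question from how clinical significance is defined.

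**Conclusion.** Wrong as written; should be fixed. Section 10.4.2 gives one criterion for two different properties, and no other section supplies a criterion of size. With about 65 completers the GCQ label would be earned at an observed difference of about 2.2 to 4.0 points (ρ from 0.7 to 0, compound symmetry, no period or carryover effect). The figure is about 3.3 to 3.7 points (ρ from 0.7 to 0.5) if the effect varies between patients with an assumed SD of 10. These compare with a planned 10.31 points. The exact values depend on a correlation that the protocol does not state, but the conclusion does not: the rule has no size component under any of them. The consequence is confined to how results are labelled and interpreted.

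**What to change.** In section 10.4.2, limit the two-sided 5% level to statistical significance and state that the home-hospital difference will be reported with its 95% CI. Then choose one of two courses.

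- Make no claim of clinical significance.
- Before unblinding, prespecify a justified GCQ threshold with its source, and a rule for using it. One example is to claim clinical relevance only when the lower 95% confidence limit for the benefit of home refills is at or above the threshold.

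The planning difference of 10.31 should not become the threshold by default. It is an assumed true effect, and if it is exactly right about half of all estimates will fall below it. Nor should the rule merely withhold the claim when the interval lies wholly below the threshold, because that rewards imprecision. Against 10.31, for example, an estimate above 10.31 − 2.81 = 7.50 would escape at ρ = 0.5, and one above 10.31 − 3.97 = 6.34 at ρ = 0.

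For secondary outcomes, use sourced, instrument-specific thresholds or make no clinical claim.

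The cost is a sentence or two and, if a threshold is adopted, the work of justifying it. No new data or patients are needed. Some statistically significant results will read less favourably: under the lower-limit rule the estimate must exceed the threshold by roughly 2.2 to 4.0 points, the half-widths found above for ρ from 0.7 to 0.

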### *Health economic analysis*

A within-trial health economic evaluation will be conducted to assess the cost-effectiveness of home-based intrathecal pump refills compared to standard outpatient clinic refills. The analysis will include all participants, covering the period up to just before the third refill procedure. Each participant will receive one refill at home and one in the outpatient clinic, with a follow-up period of approximately 2–3 months between the refills.

The analysis will follow the intention-to-treat principle (79). Data on resource use will be collected through telephone interviews, as described in the outcome section ‘health expenditure’. The valuation of resource use will be based on official Belgian national tariffs.

Health outcomes will be assessed in two ways:

1. Percentage increase in comfort, as measured by the General Comfort Questionnaire, is the trial’s primary outcome.
2. Utility values, derived from EQ-5D questionnaires and converted using Belgian population-based value sets, in line with national health economic guidelines (55).

The outpatient refill procedure will serve as the control group. Any missing data will be addressed before analysis using appropriate methods for handling incomplete health economic data (79).

Cost differences between the two groups will be analyzed using generalized linear models. The Modified Park Test will guide the selection of the appropriate model specification (80). The main result will be the Incremental Cost-Effectiveness Ratio (ICER) (81), calculated with the estimation:

$$ICER = \frac{(\text{incremental cost})}{(\text{percentage increment in functioning})}$$

and

$$ICER = \frac{(\text{incremental cost})}{(\text{incremental QALY gained})}$$

To account for uncertainty, probabilistic sensitivity analysis will be conducted (79). Non-parametric bootstrapping will be used to assess variability in cost and outcome estimates. These results will be illustrated using Cost-Effectiveness Acceptability Curves (CEACs), showing the probability that the intervention is cost-effective at various willingness-to-pay (WTP) thresholds. All results will be reported in accordance with the Consolidated Health Economic Evaluation Reporting Standards (CHEERS) guidelines (82).

In addition to the within-trial economic evaluation, a model-based analysis will be conducted to estimate the long-term costs and health outcomes of the intervention (home-based refills) versus the control (outpatient refills) beyond the trial follow-up period.

A Markov model will be developed in accordance with established health economic modelling guidelines. The model will use a one-year cycle length and a lifetime horizon to capture all relevant long-term effects. Lifetime incremental costs and QALY's will be calculated for both the home-based and outpatient refill procedures. Discount rates of 3% for costs and 1.5% for utilities will be applied, this is in line with the Belgian health economic guidelines (83,84).

The model will include probabilistic sensitivity analysis to account for parameter uncertainty, following the same approach as the within-trials evaluation. Again, results will be visualized using CEACs to illustrate the probability that the home-based intervention is cost-effective at various WTP thresholds. All modeling results will be reported in line with the CHEERS reporting standards (82).

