| Data to be collected:       | 
 
- Patient comfort – General Comfort Questionnaire (GCQ)
 
- Quality of Life (QoL) – McGill Quality of Life Questionnaire (MQOL) and EuroQol (EQ-5D-5L)
 
- Pain intensity – Visual Analogue Scale (VAS)
 
- Pain interference – Patient-Reported Outcomes Measurement Information System
 
- Stress – saliva samples with synthetic salivettes (Sarstedt AG & Co., Nümbrecht, Germany)
 
- Patient anxiety – State Trait Anxiety Inventory (STAI)
 
- Self-efficacy – General Self-Efficacy (GSE) Scale
 
- Caregiver burden – Zarit Burden Interview (ZBI)
 
- Patient satisfaction – Seven-point Likert-scale
 
- Tele-monitoring quality
 
- Time of the refill
 
- Safety
 
- Health expenditure
 
- Patient preference
 
 |
| Endpoints:                  | 
The primary endpoint is to observe whether there is a difference in the scoring of the General Comfort Questionnaire between patients with chronic non-cancer pain or spasticity after receiving a pump refill at home versus in the hospital. Each patient will receive two pump refills at home and two in the hospital.
 
The secondary outcome is whether the two arms differ on quality of life (QoL), pain intensity, pain interference, stress, anxiety, self-efficacy, burden of caregivers for patients who receive IDD, patient satisfaction, consultation time, safety, health expenditure, and patient preference. A mixed model analysis will be used with timepoints at baseline and after each refill.
                                                                                                                              |

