## Study Objectives and Endpoints

### Primary Objective

The primary objective of this study is to evaluate if intrathecal pump refills at home are better for patient comfort compared to intrathecal pump refills at the hospital. The primary outcome measure, i.e. patient comfort, is evaluated with the General Comfort Questionnaire (GCQ).

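### Section 10.4.3 calls a percentage increase in comfort the primary outcome and uses a percentage as the comfort ICER denominator, although the protocol elsewhere uses the GCQ score and a difference in points

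*Protocol*

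**What the plan says.** Four places in the protocol treat the primary outcome as a score.

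- **Section 4 (summary, Endpoints):** the primary endpoint "is to observe whether there is a difference in the scoring of the General Comfort Questionnaire between patients" after refills at home and in hospital.
- **Section 6.1 (Primary Objective):** the primary outcome measure is patient comfort, evaluated with the GCQ. No percentage is mentioned.
- **Section 6.3.1 (Primary outcome):** the GCQ is "a self-reported instrument consisting of 48 items that reflect the physical, spiritual, environmental and social dimension". "Responses are rated on a four-point Likert scale ranging from" strong disagreement to strong agreement. Some items are reverse scored, and a higher overall score means more comfort. The numeric item codes are not given; a scoring source is cited.
- **Section 11.3 (Sample size calculation):** the trial is planned "with estimated true mean comfort responses for the outpatient clinic refill of 78.47 and 88.78 for the refill at home", with an SD of 16.01049 and power for a difference in means.

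Section 10.4.3 differs. Its list of health outcomes for the economic evaluation begins "Percentage increase in comfort, as measured by the General Comfort Questionnaire, is the" trial's primary outcome. The denominator of the first ICER is then a "percentage increment in functioning". The section does not say what the percentage is relative to, or whether it is formed per patient or from group means. It names the outpatient refill as the control, and it limits the economic analysis to the period up to just before the third refill.

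**The concern.** Read literally, section 10.4.3 makes a different variable the primary outcome from the one that the rest of the protocol defines. The word percentage is unlikely to be a mere slip, because it returns in the ICER formula, this time attached to functioning, which is not the name of any outcome in the protocol. Correcting that one word would leave the percentage in place.

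A percentage needs a meaningful zero. A total over four-point agreement items has none, because the zero depends on how the answer categories are numbered. The same answers and the same costs can then give different costs per percent of comfort, and a different acceptability curve. A percentage formed within patients raises a further problem, because the hospital score is itself measured with noise and would stand in the denominator. The ICER is described as the main result of the economic evaluation, so its denominator should not depend on such choices.

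**Working it through.** **Inputs.** From section 11.3: hospital mean 78.47, home mean 88.78, SD 16.01049. From section 6.3.1: 48 items with four answer categories. Assumed, because the protocol does not state them: that the GCQ score is the sum of its items, that 78.47 is such a sum, and the correlation ρ between a patient's home and hospital scores.

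**The plan's own figure.** The plan gives no percentage to reproduce. Its planned effect is in points: 88.78 − 78.47 = 10.31.

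**Step 1: dependence on the origin.** Renumbering each item from 1-4 to 0-3 lowers every total by 48 and leaves the difference at 10.31. Possible totals run from 48 to 192 under 1-4 coding and from 0 to 144 under 0-3 coding. The planning mean of 78.47 lies inside both ranges, so it does not reveal the coding.

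| Hospital mean used as base | Percentage increase |
|---|---|
| 78.47, as stated | 10.31 / 78.47 = 13.1% |
| 78.47 − 48 = 30.47 (1-4 codes rescored 0-3) | 10.31 / 30.47 = 33.8% |
| 78.47 + 48 = 126.47 (78.47 zero-based, rescored 1-4) | 10.31 / 126.47 = 8.2% |

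For a fixed incremental cost, the cost per 1% of comfort changes by a factor of 78.47 / 30.47 = 2.6 in the first rescoring and 126.47 / 78.47 = 1.6 in the second. The cost per point does not change.

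**Step 2: percentage per patient on the hospital score, with no true difference.** For (home − hospital) / hospital with equal means and SDs, the delta method gives an expected value of about CV² × (1 − ρ). Here CV² = (16.01049 / 78.47)² = 0.0416.

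| Assumed ρ | Delta method | Simulation (4 million pairs, normal, floor at 48) |
|---|---|---|
| 0.3 | 0.0416 × 0.7 = +2.9% | +3.0% |
| 0.5 | 0.0416 × 0.5 = +2.1% | +2.1% |
| 0.7 | 0.0416 × 0.3 = +1.2% | +1.3% |

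A two-patient example shows the mechanism. Hospital/home scores of 60/90 and 90/60 have a mean difference of 0, but the mean percentage is (50 − 33.3) / 2 = +8.3%.

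**Step 3: other ways to form the percentage.** With equal true means, the ratio of mean scores stays within 0.1 percentage points of zero in simulation. With each patient's baseline score as the base, both locations carry the same upward shift (about +2.0% each at ρ = 0.5), so it cancels in the comparison. The lean towards home in step 2 therefore belongs to one construction only. The origin dependence in step 1 also affects the ratio of means.

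**The case against.** The strongest reply is that the sentence stands in a list of effect measures for the economic evaluation. Its natural meaning is that comfort on the GCQ, which is the primary outcome, will be the first of these. A reader might infer from the literal wording that the trial has two competing primary outcomes and that its main test is compromised. The documents do not support that. Sections 4, 6.1, 6.3.1 and 11.3 agree on the score, and neither the mixed model in section 10.4.2 nor the sample size uses a percentage.

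A reader might also infer that the comfort ICER is biased in favour of home. That does not follow either. Section 10.4.3 does not say that the percentage is formed per patient on the hospital score, an ICER is usually a ratio of group-level increments, and step 3 shows two constructions without the bias.

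Third, the coding may not be open at all. The protocol cites a scoring source that is not available here, only one coding can be in force, and 78.47 comes from a cited study whose scoring cannot be checked. The 1.6- and 2.6-fold changes therefore show how sensitive the measure is; they are not an error in any result. A percentage of the scale range would escape the problem, at 10.31 / 144 = 7.2% under either coding, but the plan does not define its percentage that way.

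These replies limit the point to one section. They do not remove the conflicting sentence, the undefined percentage or the mislabelled denominator.

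**Conclusion.** The point holds for section 10.4.3 only. Its wording conflicts with the definition of the primary outcome elsewhere, and the comfort ICER rests on a percentage whose base is not defined. The primary analysis and the sample size are unaffected if the score definition governs.

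If the score is a 48-item sum, the planned 10.31 points read as 13.1%, 33.8% or 8.2% of the hospital mean, depending on the numbering of the answer categories. The bias towards home, about +1.3% to +3.0% for an assumed correlation of 0.7 to 0.3, is conditional on a per-patient percentage with the hospital score as base. The correlation changes its size but not its sign. The cost-per-QALY ICER is not touched by any of this.

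**What to change.** In section 10.4.3:

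- State that the GCQ total score is the trial's primary outcome.
- Replace both percentage terms, in the outcome list and in the ICER formula, by the mean difference in GCQ total score in points, home minus hospital.
- Define the comfort ICER as incremental cost per GCQ point.
- Estimate that difference in the same patients and over the same window as the costs, namely the first two refills up to just before the third, and bootstrap the two jointly.

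The last item matters because the primary mixed model draws on assessments after all four refills. Taking its estimate into the ICER would set costs from the first two refills against an effect from four.

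The cost is one or two sentences of rewording, with no new data. Results are then read as cost per point instead of cost per percent.

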| Assessment                       | 
Saliva samples will be obtained with synthetic salivettes (Sarstedt AG & Co., Nümbrecht, Germany) at three different time points: five minutes before the refill, just after the refill and ten minutes after the refill.
 
Immediately after the termination of the teleconnection, the patient will receive a tablet with a link to the relevant questionnaires in the data collection tool. The test order will be randomized, but all will include: GCQ, MQOL, EQ-5D-5L, VAS, PROMIS, STAI, Likert-scale for patient satisfaction, GSE and questions about safety. Additionally, caregiver burden will be assessed using the ZBI. The quality of telemonitoring, duration of the consultation, and safety will be monitored by the researchers (at home and at the hospital).
 
All the above-mentioned data is study-specific, assessment does not occur during routine practice.
                                                                                                                                                                                                                                                                                                                                                                                                                                                   |

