## Tables and Figures

| What? | Patient comfort *                                                                                                                                                    | QoL *        | Pain Intensity * | Pain interference * | Stress *          | Anxiety * | Self-efficacy * | Burden caregivers * | Patient satisfaction | Tele-monitoring quality** + time | Safety                                                    | Health expenditure *** | Patient preference    |
|-------|----------------------------------------------------------------------------------------------------------------------------------------------------------------------|--------------|------------------|---------------------|-------------------|-----------|-----------------|---------------------|----------------------|----------------------------------|-----------------------------------------------------------|------------------------|-----------------------|
| How?  | GCQ                                                                                                                                                                  | MQOL + EQ-5D | VAS              | PROMIS              | Sarsted t AG & Co | STAI      | GSE             | ZBI                 | Likert-scales        | Likert-scales + time expenditure | Overall safety + environmental safety + sterile procedure | Phone calls            | Multiple choice + DCE |
| When? | At baseline * and after each intrathecal pump refill (** only applicable for refills at home)
***Four weeks after first refill and four weeks after second refill |              |                  |                     |                   |           |                 |                     |                      |                                  |                                                           |                        | After last refill     |
| Who?  | Patient                                                                                                                                                              | Patient      | Patient          | Patient             | Salivary sample   | Patient   | Patient         | Caregiver           | Patient              | Researchers                      | Patient + researchers                                     | Patient                | Patient               |

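### The within-trial cost-per-QALY analysis has no EQ-5D value inside either 2–3 month interval, so its result would rest on a convention rather than on measured utilities

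*Protocol*

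**What the plan says.** Section 10.4.3 sets the window of the within-trial evaluation as "covering the period up to just before the third refill procedure". In that window each participant has one home and one outpatient refill, "with a follow-up period of approximately 2–3 months between the refills". The second health outcome is "Utility values, derived from EQ-5D questionnaires and converted using Belgian population-based value sets", and it feeds an ICER per QALY gained.

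The EQ-5D schedule appears in three places. Section 6.3 has the baseline measures repeated after every refill. Table 1 (section 15) gives the timing as "At baseline * and after each intrathecal pump refill". Section 9.2 says of a home refill: "Immediately after the termination of the teleconnection, the patient will receive a tablet with a link to the relevant questionnaires"; at the hospital the tablet follows the consultation. The telephone calls four weeks after refills 1 and 2 (sections 6.3 and 6.3.2, Health expenditure) list consultations, admissions, adverse events, medication and other costs. EQ-5D is not among them.

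Section 7.2 groups refills in pairs, one at each location, which gives four tracks.

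The first health outcome in section 10.4.3 is "Percentage increase in comfort, as measured by the General Comfort Questionnaire". The matching ICER formula divides by "percentage increment in functioning".

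**The concern.** A QALY is utility accumulated over time. Here the time is 2–3 months per refill, while every post-baseline utility is taken within minutes of a procedure. The protocol's own case for home refills (sections 5.1.4 and 5.2) rests on travel pain, dependence on transport and the stress of the hospital visit. These may act mainly around the refill day or may last longer, and the schedule cannot show which.

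The pairing makes this worse. The next utility after refill 1 is taken after a refill at the other location, so it cannot serve as the end value of the first location's interval.

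Section 10.4.3 calls the ICER the main result of the economic evaluation, and the same utilities could feed the lifetime Markov model. Utilities that are never collected cannot be recovered by a later analysis plan.

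The comfort/functioning mismatch is a smaller matter: a contradiction within one section, in the formula for that main result.

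**Working it through.** **Inputs**
- Expected utilities (section 5.1.5): hospital 0.4523; home 0.4658, described as 3% higher.
- Interval length T (section 10.4.3): 2 to 3 months, i.e. 2/12 to 3/12 year.
- Tracks (section 7.2, pairs): with H = home and O = outpatient, HOHO, HOOH, OHHO, OHOH. Equal allocation is assumed, as no ratio is stated.
- Planned comfort means (section 11.3): 78.47 hospital, 88.78 home.

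**The plan's own figure.** 0.4523 × 1.03 = 0.46587, given as 0.4658, so it reproduces apart from truncation. The difference is 0.4658 − 0.4523 = 0.0135. The two ICERs in section 5.1.5 cannot be reproduced because their cost inputs are not given.

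**(a) Carry each post-refill value forward over its interval.** 0.0135 × 2/12 = 0.00225; 0.0135 × 3/12 = 0.00338 QALY.

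**(b) Linear interpolation, interval 1 only.** The area is T × (u1 + u2)/2, where u1, u2, u3 are the utilities after refills 1, 2 and 3. Starting at home gives T × (H + O)/2; starting at the hospital gives T × (O + H)/2. The contrast is exactly 0.

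**(c) Linear interpolation, interval 2 closed with the refill 3 value.** That value lies outside the stated window. Interval 2 has area T × (u2 + u3)/2. Home minus hospital, within track:

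| Track | Home interval | Hospital interval | Difference |
|---|---|---|---|
| HOHO | T(H+O)/2 | T(O+H)/2 | 0 |
| HOOH | T(H+O)/2 | T·O | T(H−O)/2 |
| OHHO | T·H | T(O+H)/2 | T(H−O)/2 |
| OHOH | T(H+O)/2 | T(O+H)/2 | 0 |

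The mean is (0 + 1/2 + 1/2 + 0)/4 = 1/4 of T(H−O). This gives 0.00225/4 = 0.00056 and 0.00338/4 = 0.00084 QALY.

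**(d) Effect of limited duration (assumed range).** 0.0135 × days/365:
- 1 day: 0.00004
- 7 days: 0.00026
- 28 days: 0.00104

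At a fixed incremental cost, moving from (a) to (c) multiplies the ICER by four, and under (b) it is undefined. The post-refill utilities are the same in all three.

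**Comfort.** With the planned means, (88.78 − 78.47)/78.47 = 10.31/78.47 = 13.1%. No planned value exists for functioning. Section 6.3.1 gives 48 four-point items, "with higher overall scores indicating greater levels of comfort", but no numeric codes. Shifting every item code by c leaves the difference at 10.31 but turns the percentage into 10.31/(78.47 + 48c). The point difference does not depend on that choice; the percentage does.

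**The case against.** Incremental QALYs are the standard denominator of a cost-utility ratio, and a protocol may leave the conversion from utilities to QALYs to an analysis plan. Both points stand: the formula is not at fault, and no conversion method is required here. The protocol also does not commit to interpolation. By attaching one utility to each location, section 5.1.5 hints at carry-forward, though only in the background. What remains is the measurement schedule, which is protocol content. Baseline EQ-5D does not fill the gap, because it precedes randomization and holds no information on location. The telephone interview form is not shown, but neither the listed call content nor Table 1 places EQ-5D there.

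Three stronger readings are tempting and are not supported.
- A reader might infer that the QALY gain is overstated 61- to 91-fold. That is carry-forward over 61–91 days set against an effect lasting one day. Nothing in the protocol supports one day; 7 or 28 days give much smaller gaps.
- A reader might infer that the first ICER needs an outcome the trial lacks. The two formulas follow the order of the two listed outcomes, so functioning is evidently a slip for comfort.
- A reader might infer a specific distortion from item coding. If 78.47 were on 1–4 coding, recoding to 0–3 would give 10.31/30.47 = 33.8%; if it were on 0–3 coding, recoding to 1–4 would give 10.31/126.47 = 8.2%. The coding behind 78.47 is not stated, so neither figure can be claimed. With one scoring used throughout, the percentage does not change the direction of the result.

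**Conclusion.** The point holds for the EQ-5D schedule. No utility is planned within either interval, and none closes interval 2 inside the window. With the protocol's gain of 0.0135, the incremental QALY is 0 (interpolation, interval 1), 0.0006–0.0008 (interpolation closed at refill 3) or 0.0023–0.0034 (carry-forward), depending only on convention. The 25% figure assumes four equally likely tracks, a constant utility per location and a refill 3 value from outside the window. The 1-, 7- and 28-day results rest on assumed durations.

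The formula wording is a minor inconsistency to reconcile. Both matters concern the economic objective. The primary GCQ comparison is not touched.

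**What to change.** Add the telephone version of EQ-5D-5L to the existing calls four weeks after refills 1 and 2, and enter it in Table 1. Use those values for the interval QALYs and say how they are applied up to the end of each interval. Keep the post-refill EQ-5D as a refill-day outcome. If a pre-refill EQ-5D is also wanted to close an interval, it should be completed at home before any travel; otherwise it would carry the travel effect of the next location.

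The cost is a five-item questionnaire at two calls already planned: 2 × 82 = 164 administrations at the target sample size. The small downside is mixed administration mode (telephone alongside tablet). The change is needed early, since missed values cannot be collected later.

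In section 10.4.3, replace functioning in the first ICER with GCQ comfort, preferably as incremental cost per GCQ point using the mean within-patient home–hospital difference. If a percentage is kept, define its reference value and state the item coding. This is a wording change only.
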